## Abstract

**Introduction:**

Numbers of patients undergoing mitral valve repair (MVr) surgery for severe mitral regurgitation have grown and will continue to rise. MVr is routinely performed via median sternotomy; however, there is a move towards less invasive surgical approaches.

There is debate within the clinical and National Health Service (NHS) commissioning community about widespread adoption of minimally invasive MVr surgery in the absence of robust research evidence; implementation requires investment in staff and infrastructure.

The UK Mini Mitral trial will provide definitive evidence comparing patient, NHS and clinical outcomes in adult patients undergoing MVr surgery. It will establish the best surgical approach for MVr, setting a standard against which emerging percutaneous techniques can be measured. Findings will inform optimisation of cost-effective practice.

**Methods and analysis:**

UK Mini Mitral is a multicentre, expertise based randomised controlled trial of minimally invasive thoracoscopically guided right minithoracotomy versus conventional sternotomy for MVr. The trial is taking place in NHS cardiothoracic centres in the UK with established minimally invasive mitral valve surgery programmes. In each centre, consenting and eligible patients are randomised to receive surgery performed by consultant surgeons who meet protocol-defined surgical expertise criteria. Patients are followed for 1 year, and consent to longer term follow-up.

Primary outcome is physical functioning 12 weeks following surgery, measured by change in Short Form Health Survey (SF-36v2) physical functioning scale. Early and 1 year echo data will be reported by a core laboratory. Estimates of key clinical and health economic outcomes will be reported up to 5 years.

The primary economic outcome is cost effectiveness, measured as incremental cost per quality-adjusted life year gained over 52 weeks following index surgery.

**Ethics and dissemination:**

A favourable opinion was given by Wales REC 6 (16/WA/0156). Trial findings will be disseminated to patients, clinicians, commissioning groups and through peer reviewed publication.

**Trial registration number:**

ISRCTN13930454.

Strengths and limitations of this studyLargest randomised controlled trial of minimally invasive cardiac surgery globally.Strong and ongoing patient and public involvement and international clinical consensus informed trial design.Robust design, with 90% power, includes randomisation to surgery performed by consultant surgeons with defined expertise beyond the learning curve. Design requires some patients to move between surgeons, which may impact recruitment but assures quality of outcomes and reduces bias.Multicentre UK trial with blinding of central primary outcome assessor and echocardiogram core laboratory.Up to 5 year estimates of key clinical and survival outcomes.

## Introduction

Mitral regurgitation is most commonly caused by degenerative mitral valve disease, which leads to dilatation of the mitral valve annulus, leaflet prolapse or leaflet restriction. It can also be caused by rheumatic valve disease, or infective endocarditis.

Mitral valve repair (MVr) surgery is the optimal treatment for patients with severe mitral regurgitation caused by degenerative disease; when compared with mitral valve replacement, it carries a lower perioperative mortality, improved survival, better preservation of left ventricular function and lower long-term morbidity and mortality.^1–6^

MVr surgery for mitral valve regurgitation is frequently performed^7^ and patient numbers in the UK increased by a third between 2003 and 2012 (from 1549 to 2118^8 9^; the number of patients undergoing isolated MVr surgery more than doubled over the same time (681 in 2003 to 1456 in 2012)).^8 9^ The rise is expected to continue. Furthermore, international guidance recommends that asymptomatic patients may benefit from early surgery.^10^

### Choice of comparators

Mitral valve surgery is routinely performed via sternotomy which involves dividing the sternum completely, enabling easy access to the heart and cannulation of the great vessels centrally to establish cardiopulmonary bypass. It allows flexibility in myocardial protection strategies and potentially simplifies deairing and haemostasis at the end of the procedure.

Disadvantages of a sternotomy incision include an increase in bleeding because of the size of the incision.^11^ The mitral valve is posterior to the incision and valve access can be difficult. Wound infections occur in 2%–3% of patients, and significant morbidity, and mortality, can result from this complication.^12 13^ The sternotomy incision is usually closed using multiple stainless steel wires facilitating immobilisation of the sternum while sternal union occurs. It can take up to 3 months for the sternum to heal completely.^12^ During this period, the activity of patients is significantly limited to reduce the risk of sternal dehiscence. These limitations can reduce the speed of recovery and limit patients’ ability to return to usual activities. Moreover, limited activity during this period can increase the risk of complications in the recovery period.

Minimally invasive approaches are increasingly used in all surgical specialties. In cardiac surgery, they are routinely used for coronary revascularisation^14^ aortic valve surgery, aortic root surgery^15^ and surgery for assist devices.^16^

Several publications have established the safety of minimally invasive mitral valve surgery.^17–22^ Outcomes in a cohort of 1000 patients undergoing minimally invasive mitral valve surgery between 2003 and 2011 demonstrated a mortality of 0.7% at 1 year, and 8 year survival of 90%.^18^ Of those surviving, freedom from reoperation at 8 years was 93%.^18^ The approach may also significantly reduce morbidity and mortality in high-risk patients including in the elderly.^19–21^ A propensity matched analysis of 2400 cases from 3 UK centres suggested a reduction of blood transfusion (20.5% vs 14.4%, p=0.005) and median length of hospital stay (7 vs 6 days, p<0.001) when minimally invasive surgery was compared with conventional surgery despite longer procedural times.^22^

There is emerging evidence from non-NHS healthcare settings that the minimally invasive approach is less costly than conventional sternotomy; with cost savings driven by reduced intensive care and hospital stay as well as reduced need for blood transfusion.^23^

### Current evidence supporting the rationale for the trial

Five published meta-analyses compare minimally invasive with conventional MVr.^24–28^ These identify only two small randomised controlled trials (RCTs) reporting short-term^29^ and long-term^30^ outcomes and base their main conclusions on evidence from observational studies;^18 19 23 31–38^ these provide no evidence of differences in clinical outcomes. The literature is severely limited by the absence of robust data on comparative outcomes between the two techniques.^24–28^

The International Society of Minimally Invasive Cardiac surgery published a consensus document on the role of minimally invasive mitral valve surgery in contemporary cardiac surgery practice in 2010.^39^ This highlights the limitations of available evidence in reaching a consensus, particularly the lack of adequately powered prospective RCTs to establish the comparative effectiveness of the two approaches. Its recommendation was for further prospective RCTs, adequately powered to assess quality of life, complications, efficacy (repair rates) and clinically relevant outcomes, particularly long term survival, patient functionality and freedom from re-operation.^39^

Less than 5% of patients having mitral valve surgery in the UK currently have a minimally invasive MVr, largely as a result of the lack of clear and definitive evidence. There is consensus in the cardiac surgery community that the optimum surgical approach to treat these patients urgently needs defining. This is particularly pressing as there is emerging evidence relating to the effectiveness of percutaneous MVr with the mitraclip and other devices in degenerative^40^ and functional mitral regurgitation.^41^ It is now clear that trials of percutaneous approaches and surgery are needed, but cannot be undertaken until the optimal surgical approach is clearly defined.

## Methods and analysis

### Study design

UK Mini Mitral is a multicentre, RCT of minimally invasive thoracoscopically-guided right minithoracotomy (intervention) versus conventional sternotomy (control) in patients undergoing MVr. The trial includes an internal pilot to assess the likelihood of meeting recruitment targets.

The trial will answer the questions ‘Are improvements in physical functioning and associated return to usual activities seen in patients who undergo minimally invasive mitral valve surgery compared with conventional surgery?’ and ‘Is minimally invasive mitral valve surgery compared with conventional surgery cost-effective?’

### Setting

Three hundred and sixteen patients due to receive MVr surgery will be recruited from UK NHS cardiothoracic surgery units with established minimally invasive and conventional mitral valve services. All centres will be able to accommodate the needs of this trial including established minimally invasive MVr services, research nurse and echocardiographer support, and facilities to carry out trial assessments. Only units in equipoise in the way they manage their patients requiring MVr will participate.

At each centre, individual surgeons perform one type of operation; MVr via thoracoscopically guided right minithoracotomy or MVr via median sternotomy. Before performing surgery within the trial, each surgeon has completed 50 of these; the Trial Steering Committee (TSC) reviews a record of the number of operations for each surgeon, and agrees to their participation, in advance of them doing so. Depending on their allocation, patients can be required to move to another surgeon following randomisation.

### Eligibility criteria

Patients are eligible to take part if they are scheduled to have surgery for MVr and fulfil all eligibility criteria:

#### Inclusion criteria

Adult (≥18 years old at consent) with degenerative mitral valve disease, requiring MVr*.Written informed consent.Fit for cardiac surgery and cardiopulmonary bypass.

*Patients requiring concomitant surgery for atrial fibrillation (AF), tricuspid valve repair, and/or patent foramen ovale (PFO) closure are included

#### Exclusion criteria

Concomitant cardiac surgery other than for AF, tricuspid valve repair and PFO closure.Requiring mitral valve replacement.Acute (current) infective endocarditis.Emergency or salvage surgery.Only one surgical technique indicated.Pregnant.**Currently participating in another interventional clinical trial.≥ 4 weeks as an inpatient prior to randomisation.Previous cardiac surgery.Mobility impairments that would preclude Short Form Health Survey (SF36-v2) completion.

**Female patients between the ages of 18 and 50 will receive a pregnancy test at baseline.

### Randomisation

Eligible patients will be randomised in a 1:1 ratio to undergo MVr using minimally invasive thoracoscopically guided right minithoracotomy (intervention under study) or conventional median sternotomy (control arm/usual care) by members of the research team at each centre using a 24-hour, central, secure, web-based randomisation system with concealed allocation (procured from Sealed Envelope).

Randomisation is performed using a minimisation scheme, which adjusts for baseline SF-36v2 physical functioning score, presence or absence of AF and/or PFO, and presence and severity of tricuspid regurgitation.

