### Sample size

The primary outcome measure is change in physical functioning scale within SF-36v2^42^ from baseline to 12 weeks following index surgery. On the basis of the literature and consulting with cardiac and patient communities, a minimally clinically important difference is 10 points on the scale. UK Mini Mitral is powered to investigate the superiority of thoracoscopically guided right minithoracotomy over conventional sternotomy.

One study^31^ reports a small variation (SD of 8) in SF-36 physical function scores; this is not seen in other studies^32 33^ which report a SD of 30. We used the conservative estimate to inform the original sample size calculation:

Assuming alpha of 5% and 90% power, 382 patients (191 in each arm) would be required to detect a minimally clinically important difference of 10 points in the SF-36v2^42^ physical functioning scale at 12 weeks (assuming SD of 30); allowing for attrition, we planned to randomise 400 patients. To assess our assumptions, we performed a blinded sample size re-estimation using baseline SF-36v2 physical functioning scale data from 177 trial patients. Using the re-estimated SD of 26.3 with 90% power, 288 patients are required to detect a 10 point difference in SF-36v2 physical functioning at 12 weeks. Accounting for 10% attrition, 316 patients will be recruited.

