### Trial procedures

Patients due to undergo isolated MVr surgery at participating centres are identified at the point of referral (elective patients) and from the inpatient waiting list (urgent but non-emergency patients) by the clinical research team and approached about the trial, including given an information sheet and consent form. After discussion, consent is sought, baseline assessments performed and eligibility checked and confirmed by one of the consultant surgeons participating in the trial. Eligible patients are randomised, and their general practitioners informed. A full schedule of events is detailed in table 1, and a participant flow chart provided in figure 1. Patients have assessments at 6, 12, 18, 24, 38 and 52 weeks following index surgery. Longer term follow-up will involve routinely collected data.

**Table 1 T1:** UK Mini Mitral Schedule of Events

Study procedure	Baseline	Day of surgery	Index hospital stay	Follow-up: time is calculated from the day of index surgery					
	−26 weeks to day of surgery	Day 0	Day 0 until discharge following index surgery	6 weeks	12 weeks	18 weeks	24 weeks	38 weeks	52 weks
Consent	X								
Medical history	X								
Physical examination	X								
Demographics	X								
Concomitant medications	X			X	X				X
Pregnancy test	X								
NYHA class	X			X	X				
ECHO (TTE)	X		X	X	X				X
TOE	X	X							
SF-36v2	X			X	X	X	X	X	X
EQ-5D-5L	X			X	X	X	X	X	X
euroSCORE		X							
Accelerometer	X			X	X	X	X	X	X
Eligibility check	X								
Randomisation	X								
MVr surgery		X							
Postoperative details			X						
Wound Pain score			X^i^	X	X				
Ward usage and date of discharge			X						
Discharge destination			X						
RBC and other blood product transfusions		X	X						
AEs and SAEs		X	X	X	X	X	X	X	X
Reoperation/further surgery		X	X	X	X	X	X	X	X
Health Care Utilisation Questionnaire				X	X	X	X	X	X
HES data				X	X	X	X	X	X
NICOR data				X	X	X	X	X	X
Medical record review				X	X	X	X	X	X

AE, adverse event; ECHO, Echocardiogram; EQ-5D-5L, EuroQol 5 Dimension 5 Level; HES, Hospital Episode Statistics; MVr, mitral valve repair; NICOR, National Institute for Cardiac Outcomes Research; NYHA, New York Heart Association; RBC, Red Blood Celleuor; SAE, serious adverse event; SCORE, European System for Cardiac Operative Risk Evaluation; SF36-v2, Short Form Health Survey; TOE, transoesophageal echocardiography; TTE, transthoracic echocardiography.

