### Accelerometer

Levels of physical activity and quality of sleep are quantified using accelerometer measures. Accelerometers are worn on patients’ non-dominant wrist nonstop for 7 consecutive days at seven timepoints (baseline, 6, 12, 18, 24, 38 and 52 weeks following index surgery). The restrictions of movement by being an inpatient means accelerometer measures are not possible for inhouse urgent patients and are not to be undertaken.

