### Statistical analysis

Primary analysis will follow intention to treat principles, with patients analysed according to randomisation, irrespective of surgical intervention received. A full statistical analysis plan will be developed and agreed with the Independent Data Monitoring and Ethics Committee (IDMEC) and TSC prior to the end of data collection.

Outcome data will be analysed at the end of the study; no interim outcome analyses are planned.

Primary analysis of change in physical functioning, measured using SF-36v2 at 12 weeks, will use a general linear model accounting for surgical intervention, baseline scores, valve pathology and concomitant surgery. Robust SE will account for intrapatient correlation due to repeated measures. A similar modelling approach will be used for the final analysis of change in physical functioning at 52 weeks.

Secondary outcomes: continuous outcomes will be analysed using a general linear model, binary outcomes will be analysed using a generalised estimating equation to account for repeated binary data over time, categorical outcomes (with more than two categories) will be analysed using baseline-category logit model, while log-rank test and frailty modelling will be used to analyse time-to-event outcomes. Analysis of all outcomes with repeated measures on the same patient will account for intrapatient correlation. Multiple imputation for secondary outcomes will be used if necessary to sensitise incomplete data. All outcomes will also be described using simple statistics to facilitate interpretation and communication of findings. Secondary analysis will also include hierarchical modelling of patients, surgeons and centres, to provide an estimate of treatment effect at each of these levels.

Each question within the SF-36v2 physical functioning scale will be scored based on the RAND scoring system.^42^ The average of the per-patient scale scores (assuming each question carries equal weight) will provide the primary outcome for physical functioning at 12 weeks.

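### The primary SF-36v2 model should include admission status (elective or in-house urgent): a small, free gain in precision, not a correction of bias

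*Protocol article*

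**What the plan says.** The Trial procedures section identifies patients at referral (elective) and "from the inpatient waiting list (urgent but non-emergency patients". The Exclusion criteria limit prior hospital stay only at the long end: "≥ 4 weeks as an inpatient prior to randomisation". The SF-36v2 is completed before randomisation (SF-36v2 and EQ-5D-5L section), and the Outcomes section gives a 4-week recall period for the 12-week outcome.

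The Accelerometer section leaves urgent inpatients out of activity measurement: "The restrictions of movement by being an inpatient means accelerometer measures are not possible for inhouse urgent patients". It makes no comparable remark about the SF-36v2.

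The Randomisation section reads "Randomisation is performed using a minimisation scheme, which adjusts for baseline SF-36v2 physical functioning score, presence or absence of AF and/or PFO", and adds tricuspid regurgitation as the last factor. The primary analysis in the Statistical analysis section "will use a general linear model accounting for surgical intervention, baseline scores, valve pathology and concomitant surgery". Admission status appears in neither list. The same section says that a full analysis plan will be agreed before data collection ends; that plan is not shown.

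**The concern.** If a stay in hospital temporarily lowers reported physical functioning, the same baseline score stands for better underlying function in an urgent inpatient than in an elective patient. A single baseline slope with no term for admission status then under-predicts the urgent patients' 12-week scores. Two things follow. The misfit stays in the residual variance. And if the urgent share differs between arms by chance, the estimate moves a little, in a way that balancing or adjusting for the baseline score does not fully remove.

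The exclusion at 4 weeks narrows this but does not close it. If the 4-week recall also applies at baseline, a patient with 27 inpatient days is eligible with 27 of 28 recalled days in hospital.

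What is at stake is precision in the primary comparison and the chance to settle the covariate list in advance. If the urgent share turns out unequal, adding the term after the data are seen would look data-driven.

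**Working it through.** **1. The plan's own figure.** The inputs are in the Sample size section: "a minimally clinically important difference is 10 points on the scale"; "Assuming alpha of 5% and 90% power, 382 patients (191 in each arm) would be required" (SD 30); and "Using the re-estimated SD of 26.3 with 90% power, 288 patients are required to detect a 10 point difference". With the two-sided formula N = 4·SD²·(1.960 + 1.282)²/10², SD 30 gives 378.3, or 380 in equal whole arms (382 with the t distribution; 382 stated). SD 26.3 gives 290.7, or 292 (288 stated, 1.4% lower). Power at 288 is 89.7%. The standard error at 288 is 26.3·√(4/288) = 3.10 points. The figures reproduce, and they take no credit for covariate adjustment.

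**2. Precision lost by omitting admission status.** The documents give neither the urgent share p nor the baseline lowering b, so both are assumed. The illustrative model has true function SD 22, baseline error SD 10, a 12-week score of 0.5 × true function + 10 × arm + noise of SD 20, and no lasting effect of urgency. There are 316 × 0.9 = 284 evaluable patients.

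- Total outcome variance within arm: 0.25·22² + 20² = 521.
- Baseline variance within admission status: 22² + 10² = 584. Covariance with outcome: 0.5·22² = 242. Slope: 242/584 = 0.41.
- Residual variance with admission status in the model: 521 − 242²/584 = 420.7.
- Residual variance without it: 521 − 242²/(584 + p(1−p)b²).

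| p | b | Variance without | Ratio |
|---|---|---|---|
| 15% | 10 | 422.9 | 1.005 |
| 15% | 30 | 437.2 | 1.039 |
| 35% | 10 | 424.5 | 1.009 |
| 35% | 30 | 446.8 | 1.062 |

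The degree of freedom spent on the extra term takes back about 0.4%. Simulation of the same model gave 1.00–1.06. At the top this is worth 284·(1 − 1/1.06) ≈ 16 patients.

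**3. Check under other assumptions.** A second simulation used N = 288, SD 26.3, an urgent share of 10% or 30%, lowering of 10–30 points and a baseline-to-12-week correlation of 0.3 or 0.5, with 2000 runs per setting. Without admission status:

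- the mean estimate was 9.84–10.07 for a true 10;
- type I error was 4.2–5.8%;
- in the worst case the mean standard error was 2.783 against 2.693 with the term (3.3% larger, variance ratio 1.07), and power was 94.1% against 95.2%.

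**4. Chance imbalance.** Under simple randomisation the 95% range of the difference in urgent share is ±1.96·√(4p(1−p)/316): ±7.9 points at 15% and ±10.5 at 35%. With arms balanced on baseline score, a 10-point difference in share moves the estimate by 0.41 × b × 0.10, which is 0.4 points for b = 10 and 1.2 for b = 30. Without that balance, the flatter slope of the misfitted model (242/788.75 = 0.31 at p = 35%, b = 30) brings the top to about 0.9. Both are small beside a standard error of about 3.1, which already covers this variation on average.

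**5. When the gain vanishes.** With baseline in the model, the coefficient on urgency is 0.41·b minus any lasting lowering of the 12-week score. If urgency lowers that score by about 0.4 times the baseline lowering, the coefficient is near zero and the term gains nothing.

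**6. An outer bound.** If the residual effect d of urgency after baseline adjustment is assumed directly, the share of variance explained is p(1−p)d²/26.3². It is 2.3% at p = 20%, d = 10 and 12.1% at p = 30%, d = 20. The latter is outside the range above: at slope 0.41, d = 20 would need a baseline lowering of about 48 points.

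**The case against.** The sections cited do not contradict one another. Omitting one prognostic covariate among many is ordinary, and the unseen analysis plan may add it. The baseline score is both minimised on and adjusted for, the exclusion at 4 weeks matches the stated recall period, and every driver of the size is assumed. If urgent patients were among the 177 whose baseline scores gave the SD of 26.3 (not stated), their spread is already in the sample size.

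Much of this stands, and it limits the point. It does not remove it, because the protocol names the primary model's covariates and the list lacks a status known before randomisation. Adjusting for the baseline score deals with lasting differences in function but not with a temporary lowering.

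Three stronger readings might be inferred, and the documents support none of them.

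- *Inpatient and elective SF-36v2 scores are not comparable.* The protocol says something of this kind only about accelerometry. Carrying it over to the questionnaire, and applying the 4-week recall to baseline, are inferences.
- *The primary estimate is biased or its test invalid.* Randomisation keeps the estimate unbiased, and the simulated type I error is close to 5%.
- *The minimisation is defective because urgency is missing.* Chance imbalance in an unlisted factor is normal sampling variation. The imbalance range in the working is also somewhat too wide: it assumes simple randomisation, whereas balancing the baseline score would partly balance urgency if the two are related.

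**Conclusion.** The point holds as a minor efficiency improvement. The stated primary model leaves out a baseline status that may change what the baseline score means. The avoidable loss is about 0–6% of the variance of the treatment effect for an urgent share of 15–35%, a baseline lowering of 10–30 points and no lasting effect at 12 weeks; a somewhat different set of assumptions gives at most about 7%. It may be nil. The trial keeps about 90% power under its own assumptions whether or not the term is added. Severity is low. The case for acting is that the change costs almost nothing and is cleanest when made before the data are seen.

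**What to change.** In the analysis plan, add admission status at randomisation (elective or in-house urgent) as a covariate in the primary 12-week model and in the other SF-36v2 models. Pre-specify one sensitivity analysis with a baseline-by-status interaction, so that the baseline slope can differ between the two groups. Report the number of urgent patients by arm. If the plan already does this, nothing further is needed.

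The cost is one line of text and one degree of freedom in the main model, plus one more in the sensitivity analysis. Status must already be known for each patient to decide whether accelerometry applies, so no new data collection is expected. The randomisation system stays as it is.
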